##### 8.3.1.2.4. Pittsburgh Sleep Quality Index (PSQI)

PSQI aims to assess a person’s sleep quality with questions relating to their sleeping habits within the past month. The PSQI consists of 18 self-rated questions and five questions raised by the bedpartner or roommate **(Table 4)**. The latter five questions are used for clinical information only, are not tabulated in the scoring of the PSQI. These 19 items are grouped into seven component scores, each weighted equally on a 0-3 scale. Higher scores indicate worse sleep quality. These components are subjective sleep quality, sleep latency, sleep duration, habitual sleep efficiency, sleep disturbances, use of sleeping medications, and daytime dysfunction over the past month. The seven-component scores are added in order to obtain a “global” score ranging from 0 to 21 points, where “0” indicates no difficulty and “21” indicates major difficulties in all areas. The global PSQI score, ranging from 0 to 21, can be collected by summing the seven components after weighting them on a scale ranging from 0 to 3. For each component, as well as the global PSQI score, higher sleep scores show worse sleep quality. The global score < 5 associated with good sleep quality while > 5 associated with poor sleep quality.

**Table 4. Scoring rule of pittsburgh sleep quality index**

| **component1**  **PSQISLPQUAL** | **OVERALL SLEEP QUALITY** | **Q6**  **Minimum Score = 0 (better); Maximum Score = 3 (worse)** |
| --- | --- | --- |
| component2 PSQILATEN | SLEEP LATENCY | **First, recode Q2 into Q2new thusly:**  IF Q2 > 0 and < 15, THEN set value of Q2new to 0  IF Q2 > 15 and < 30, THEN set value of Q2new to 1  IF Q2 > 30 and < 60, THEN set value of Q2new to 2  IF Q2 > 60, THEN set value of Q2new to 3  **Next**  IF Q5a + Q2new = 0, THEN set value to 0  IF Q5a + Q2new > 1 and < 2, THEN set value to 1  IF Q5a + Q2new > 3 and < 4, THEN set value to 2  IF Q5a + Q2new > 5 and < 6, THEN set value to 3  Minimum Score = 0 (better);  Maximum Score = 3 (worse) |
| component3  PSQIDURAT | DURATION OF SLEEP | IF Q4 > 7, THEN set value to 0  IF Q4 < 7 and > 6, THEN set value to 1  IF Q4 < 6 and > 5, THEN set value to 2  IF Q4 < 5, THEN set value to 3  Minimum Score = 0 (better);  Maximum Score = 3 (worse) |
| component4  PSQIHSE | SLEEP EFFICIENCY | Diffsec = Difference in seconds between day and time of day Q1 and day Q3  Diffhour = Absolute value of diffsec / 3600  newtib =IF diffhour > 24, then newtib = diffhour – 24  IF diffhour < 24, THEN newtib = diffhour  (NOTE, THE ABOVE JUST CALCULATES THE HOURS BETWEEN GNT (Q1) AND GMT (Q3))  tmphse = (Q4 / newtib) * 100  IF tmphse > 85, THEN set value to 0  IF tmphse < 85 and > 75, THEN set value to 1  IF tmphse < 75 and > 65, THEN set value to 2  IF tmphse < 65, THEN set value to 3  Minimum Score = 0 (better); Maximum Score = 3 (worse) |
| component5  PSQIDISTB | SLEEP DISTURBANCE | IF Q5b + Q5c + Q5d + Q5e + Q5f + Q5g + Q5h + Q5i + Q5j (IF Q5JCOM is null or Q5j is null, set the value of Q5j to 0) = 0, THEN set value to 0  IF Q5b + Q5c + Q5d + Q5e + Q5f + Q5g + Q5h + Q5i + Q5j (IF Q5JCOM is null or Q5j is null, set the value of Q5j to 0) > 1 and < 9, THEN set value to 1  IF Q5b + Q5c + Q5d + Q5e + Q5f + Q5g + Q5h + Q5i + Q5j (IF Q5JCOM is null or Q5j is null, set the value of Q5j to 0) > 9 and < 18, THEN set value to 2  IF Q5b + Q5c + Q5d + Q5e + Q5f + Q5g + Q5h + Q5i + Q5j (IF Q5JCOM is null or Q5j is null, set the value of Q5j to 0) > 18, THEN set value to 3  Minimum Score = 0 (better);  Maximum Score = 3 (worse) |
| component6  PSQIMEDS | NEED MEDS TO SLEEP | Q7  Minimum Score = 0 (better);  Maximum Score = 3 (worse) |
| component7  PSQIDAYDYS | DAY DYSFUNCTION DUE TO SLEEPINESS | IF Q8 + Q9 = 0, THEN set value to 0  IF Q8 + Q9 > 1 and < 2, THEN set value to 1  IF Q8 + Q9 > 3 and < 4, THEN set value to 2  IF Q8 + Q9 > 5 and < 6, THEN set value to 3  Minimum Score = 0 (better);  Maximum Score = 3 (worse) |
| PSQI | TOTAL | DURAT + DISTB + LATEN + DAYDYS + HSE + SLPQUAL + MEDS  Minimum Score = 0 (better);  Maximum Score = 21 (worse)  Interpretation:  TOTAL < 5 associated with good sleep quality  TOTAL > 5 associated with poor sleep quality |

Note: PSQISLPQUAL=PSQI sleep quality; PSQILATEN=PSQI sleep latency; PSQIDURAT=PSQI duration of sleep; PSQIHSE=PSQI sleep efficiency; Diffsec=difference in seconds; Diffhour=Difference in hours; GNT=gone to bed at night time; GMT=get up in the morning time; tmphse= time of sleep efficiency; PSQIDISTB=PSQI sleep disturbance; PSQIMEDS=PSQI need medicine to sleep; PSQIDAYDYS=PSQI day dysfunction due to sleepiness; DURAT=duration; DISTB=disturbance; LATEN=latency; DAYDYS=day dysfunction; HSE=sleep efficiency; SLPQUAL=sleep quality; MEDS=medicine to sleep.

##### 8.3.1.2.5. (PPT)

Pressure pain threshold (PPT) is the only test for deep-pain sensitivity, most probably mediated by muscle C- and A-delta fibers. PPT is defined as the amount of pressure at which the participant first perceived the stimulus to be painful. PPT is one of the commonly used evaluation indicators of TMD pain, which is used for quantitative description.

Trained study staff will perform the PPT measurements. An electronic pressure algometer (Somedic Sales AB, Solna, Stockholm, Sweden) will be used to assess the PPT. This device consists of a grip with a pressure-sensitive strain gauge at the tip and a display unit. The 1 cm^2^ probe tip is covered with a 1 mm thick rubber pad to minimize the risk of irritation of the skin. The algometer is held perpendicular to the skin surface over the muscles and the pressure is increased at a standardized rate of 50 kPa per second. The patient is positioned comfortably in a sitting position, with muscle relaxed. And the patients will be instructed to press a signal button when the sensation of “pressure” changed into “pain”. This was first performed over the soft tissue close to the base of the thumb on the dorsal side of the right hand, in order to accustom the subject to the procedure. The following sites are assessed: bilateral masseter muscles, bilateral anterior temporalis muscle, bilateral sternocleidomastoid, bilateral trapezius muscles and the bilateral temporomandibular joint. The values from the right and left sides will be averaged to obtain a single PPT value per anatomical site, and the average of three trials is considered the final PPT value. There is a two-minute interval between the trials at the same muscle site, and a five-second interval between the measurements of one muscle site and the other.^28^

##### 8.3.1.2.6. (sEMG)

Surface Electromyography (sEMG) is a kind of examination that reflects the state and function of the measured muscle by recording changes in electrical signals during muscle activity. The electrical activity of the anterior part of the temporal and masseter muscles is assessed in accordance with the assumptions of surface electromyography (sEMG).^29^

During the sEMG recording, the environment is kept quiet, with the subject seated in a comfortable chair with the soles of the feet flat on the ground with their arms resting on their legs. The head is positioned upright, with the patient looking toward the horizon. Prior to electrode placement, the subjects’ skin is cleaned with alcohol 75% solution, with the aim of eliminating any facial oils or pollution that could interrupt sEMG signals. Double surface electrodes of silver chloride, disposable, bipolar, with self-adhesive gel are placed on the masseter and anterior temporalis bilaterally, in the longitudinal direction of the muscle fibers. Disposable circular electrodes with an interelectrode distance of 20 mm and a ground electrode placed above the crease of the wrist.

Surface EMG was recorded using a Miotec^®^, model Miotool 400 4-channel system. The system acquired 14-bit EMG signals with electrical isolation of 3000 volts, high EMG signal representation across all channels (2000 samples/second per channel), rejection of 110 dB common mode and low noise level < 2 LSB (Low Significant Bit); EMG signals are acquired using Miograph software with 2000 Hz sampling frequency, 20-500 Hz bandpass filter with interference eliminated by the Notch Filter.

A muscle function test is performed before placing the electrodes served to identify the center of the muscles to be analyzed. The electrodes are placed parallel to the muscle origin and insertion. Before the exam, subjects are asked to perform a maximum voluntary contraction (MVC), a five-second isometric contraction of the masseter and anterior temporal muscles, in order to conduct normalization of the data, interpreted subsequently with the MATLAB. EMG signal acquisition are captured in the following three tasks: the mandibular resting position (MR), the habitual chewing (HC), and the maximum voluntary contraction (MVC). When measuring HC, Trident^®^ gum is used for 20 chewing cycles.^30 31^ Potential amplitude is expressed in microvolts (μV) and expressed by root mean square (RMS).

##### 8.3.1.2.7 ****Acupuncture Expectancy Scale****

The acupuncture expectancy scale consists of an item measuring the expectation of improvement of illness due to acupuncture treatment. Patients will be asked to rate from 1 to 5 on a five-point Likert scale, with 1 indicating “Ineffective”, 2 indicating “May be ineffective”, 3 indicating “Unclear”, 4 indicating “May be effective”, 5 indicating “Effective” with the expected improvement as result of acupuncture.

##### 8.3.1.2.8 ****Patient’s satisfaction****

The Participants’ satisfaction scale is a validated generic tool for assessment of patient satisfaction. Patients will rate how they describe the satisfaction since beginning the treatment in this study on a 5-point scale where 1=extremely dissatisfied; 2=dissatisfied; 3=moderately satisfied; 4=satisfied; 5=extremely satisfied. Participants who achieve score 4 or score 5 are considered as responders.

##### 8.3.1.2.9 Blinding assessment

To test the success of blinding, within 5 minutes after treatment at week 4, participants will be told that there are two kinds of treatment groups: “Acupuncture group” and “Sham acupuncture group”, and they will be randomly assigned to either group at 50% chance respectively. Participants will then be asked to answer the question “Do you think which kind of treatment group you have participated in during the past weeks?”The participants will be able to choose one of the following options as the answer: “Acupuncture group”, “Sham acupuncture group” or “Did not know”.

The Bang blinding indices will be used to assess the success of blinding. The Bang blinding index for each group represents the proportion of participants making a correct treatment guess beyond chance; 0 represents perfect blinding, a positive index indicates a correct guess, and a negative index indicates a guess in the opposite direction.

### 8.3.2 Secondary Efficacy Analysis

For the proportion of responders of ≥30%, ≥50% reduction in pain intensity, a logistic regression model was implemented adjusted for sex, age, weekly pain intensity (VAS) at baseline, TMD-specific medication. Mean percentage with SE, and odds ratios with 95% CIs were presented for the efficacy outcomes by 4 weeks.

The analysis of continuous secondary outcomes were performed similarly to the primary efficacy outcome. A linear regression method, which is similar to the primary analysis setup, will be used for the analysis of secondary efficacy variables change from baseline to week 4: jaw opening and movement, GCPS score, JFLS-20 score, DASS-21 score, PSQI score, PPT, sEMG. The LSM change from baseline with SE was presented for each treatment group, and the LSM with 95% CIs for the treatment differences, and associated p-values will be provided.

A corresponding sensitivity analysis will be performed on the PP set using a linear regression model or logistic regression model as specified on the ITT set.

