**1. INTRODUCTION**

**1.1 Background**

**1.1.1 Overview**

Temporomandibular Disorders (TMD) refer to a group of symptoms that may originate from the temporomandibular joint, muscles of mastication, and their associated structures,^1^ affect 5-12% of the population mainly in younger persons.^2^ It is considered the first leading cause of pain and disability among frequently occurring facial pain and the second among musculoskeletal conditions with an annual cost estimated at $4 billion.^3^ The diagnostic criteria of TMD have evolved over the last three decades to achieve the most reliable and valid diagnosis. The recent Diagnostic Criteria classify TMD (DC/TMD) into two groups, one of which is pain-related disorders (including myalgia, arthralgia, and headache attributed to TMD).^2^ Jaw pain is the most common symptom that compels patients to seek treatment, with an average TMD pain intensity rating of 5.0 on a 11-point scale in patients with TMD.^4^ In addition to facial pain, TMD patients frequently report a high level of comorbid idiopathic pain conditions such as headaches, depression, sleep disorders, and fibromyalgia.^5-7^

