### 12.6.3 Analysis of the Secondary Outcomes

For the proportion of responders of ≥30% and ≥50% reduction in weekly pain intensity, a logistic regression model was implemented adjusted for sex, age, weekly pain intensity at baseline, TMD-specific medication. Mean percentage with SE, and odds ratios with 95% CIs were presented for these efficacy outcomes by 4 weeks.

The analysis of continuous secondary outcomes were performed similarly to the primary efficacy outcome. A linear regression method, which is similar to the primary analysis setup, will be used for the analysis of the mean change from baseline in jaw opening and movement, GCPS, JFLS-20, DASS-21, PSQI, PPT, and sEMG at week 4. The LSM change from baseline with SE was presented for each treatment group, and the LSM with 95% CIs for the treatment differences, and associated p-values will be provided.

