## 3.2 Sample Size and Power Considerations

Based on our pilot study, the reduced pain intensity (VAS score) of TMD patients after 4-week treatment was 3.4±0.3 in the acupuncture group and 2.9±0.7 in the sham acupuncture group. A sample size of 50 patients gives at least 90% power for the study to succeed at an alpha level of 0.05. Assuming a 10% loss rate of follow-up, 30 patients per treatment group were planned for randomization.

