## 8.2 Primary Efficacy Variable and Analysis

For the purpose of this study, the change of pain intensity will be defined as the reduced score of weekly pain intensity (reported on a 0-10 VAS) from baseline to the last week of treatment period.

The primary statistical analysis to evaluate the primary hypothesis will use all data from the ITT analytical sample in a linear regression model. Mixed models will be used to analyze the treatment effect at Week 4.

The weekly pain intensity was calculated if a participant completed at least 4 of the 7 daily reports of pain intensity. For patients with missing days and fewer than 4 days of TMD diary data for 1 week, the weekly pain intensity was considered missing before the multiple imputation procedure. The statistics were based on 10 sets of imputed data, where the mean is the average of the means from the 10 data sets and the standard error (SE) of the mean is adjusted based on the imputation variance estimates.

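### At the planned changes the ordinary logistic model will almost certainly give no finite odds ratio for ≥30% response, and may give none for ≥50%; the SAP names no fallback

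*Combined protocol and SAP*

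**What the plan says.** SAP 8.3.1.1.1 defines a responder by a fall of at least 30% or at least 50% from baseline pain at week 4 and makes the odds ratio the summary measure. For the analysis, SAP 8.3.2 states that "a logistic regression model was implemented adjusted for sex, age, weekly pain intensity (VAS) at baseline, TMD-specific medication". Protocol 12.6.3 has the same model and adds: "Mean percentage with SE, and odds ratios with 95% CIs were presented for these efficacy outcomes by 4 weeks". Neither document says whether the interval is Wald or profile likelihood, and neither names a penalised or exact method or a difference in proportions. The model is reused on the per-protocol set (SAP 8.3.2, 8.4.3) and at week 8 (protocol 12.6.4).

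The planning changes are "3.4±0.3 in the acupuncture group and 2.9±0.7 in the sham acupuncture group" (SAP 3.2). No planned baseline mean, baseline SD or responder rate is given. The nearest figure is a background one in protocol 1.1.1: "an average TMD pain intensity rating of 5.0 on a 11-point scale in patients with TMD".

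**The concern.** When every patient in one arm responds, the data are separated: the maximum-likelihood odds ratio is infinite, its standard error is meaningless, and a Wald interval covers 1 whatever the true difference. The planned acupuncture fall of 3.4 with SD 0.3 lies far above 30% of any likely baseline, and above 50% of a baseline near 5.0 (2.5). An all-responder arm is therefore a foreseeable result.

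The two responder outcomes are the only secondary outcomes listed under the primary objective. Without a stated fallback, the method would be chosen after the data were seen. Multiple imputation could add to this. For weekly pain, SAP 8.2 says that "the standard error (SE) of the mean is adjusted based on the imputation variance estimates". If responder models are pooled in the same way, from estimates and SEs, the inference is Wald, and one separated imputed dataset can spoil the pooled result.

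**Working it through.** **Reproducing the plan's figure.** SAP 3.2 states: "A sample size of 50 patients gives at least 90% power for the study to succeed at an alpha level of 0.05". With a difference of 0.5 and a mean variance of (0.3² + 0.7²)/2 = 0.29, n per arm = 2 × (1.960 + 1.282)² × 0.29 / 0.5² = 24.4, so 25 per arm and 50 in total. Power at 25 per arm is 90.7%. Then 50/0.9 = 55.6, which the plan rounds up: "Assuming a 10% loss rate of follow-up, 30 patients per treatment group were planned for randomization". The planned changes are therefore the plan's own working values.

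**Inputs for the responder check.** Change 3.4±0.3 versus 2.9±0.7 and 30 per arm are from the SAP. Baseline mean (5 to 7), baseline SD (0 to 2) and the correlation ρ between change and baseline are assumptions. TMD-specific medication is disallowed in the trial, so it should be nearly constant and was left out of the simulated model, which adjusts for sex, age and baseline pain.

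**Formula.** With threshold c = 0.3 or 0.5,

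response rate = Φ[(mean change − c × baseline mean) / √(SD_change² + (c × SD_base)² − 2ρ·c·SD_change·SD_base)].

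The chance that all 30 acupuncture patients respond is the rate to the power 30.

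**≥30%, baseline SD 1.0, ρ = 0.**
- Mean 5.0: acupuncture Φ(1.9/√0.18) = 100.0%; sham Φ(1.4/√0.58) = 96.7%. The difference is 3.3 points. All acupuncture patients respond in essentially every trial. Both arms are complete in about 0.967³⁰ = 37% of trials.
- Mean 7.0: acupuncture Φ(1.3/√0.18) = 99.9%; sham Φ(0.8/√0.58) = 85.3%. The chance of 30/30 is 0.9989³⁰ = 97%, and the difference is 14.6 points.
- In simulation, 96-100% of trials have no finite odds ratio for means of 5 to 7. At mean 5.0, with baseline SD from 0 to 2, the true difference is 2 to 6 points and Fisher's exact test is significant in at most 0.2% of trials.

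**≥50%.** For mean 5.0 and SD 1.0, acupuncture is Φ(0.9/√0.34) = 93.9% and sham Φ(0.4/√0.74) = 67.9%, a difference of 26.0 points; 0.939³⁰ = 15%. At ρ = 0.4 the variances are 0.34 − 0.12 = 0.22 and 0.74 − 0.28 = 0.46, giving 97.2% versus 72.2%; 0.9725³⁰ = 43%. Covariates add some further separation. Simulation used 300 to 400 trials per row, with separation found by linear programming and a separated trial counted as not significant by Wald:

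| Baseline mean, SD, ρ | True response | No finite OR | Wald power | Alternative |
|---|---|---|---|---|
| 5.0, 0, – | 99.9% v 71.6% | 96% | 2.5% | LR 99% |
| 5.0, 0.5, 0 | 98.9% v 70.5% | 73% | 23% | LR 98% |
| 5.0, 1.0, 0 | 93.9% v 67.9% | 16-17% | 67-68% | Firth 86%, LR 90% |
| 5.0, 1.0, 0.4 | 97.2% v 72.2% | 47-50% | 37-38% | Firth 88%, LR 90% |
| 5.0, 1.5, 0 | 86.7% v 65.2% | 3% | 64% | LR 74% |
| 5.5, 1.0, 0 | 86.7% v 56.9% | 3% | 82% | LR 90% |
| 6.0, 1.0, 0 | 75.4% v 45.4% | 0% | 84% | LR 86% |

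LR is the unpenalised likelihood-ratio test; Firth is the penalised one. Monte Carlo error is about ±2 to 6 points.

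**Larger change SDs (baseline 5.0±1.0, ρ = 0).** For ≥50% with SD 1.0, acupuncture is Φ(0.9/√1.25) = 79%, so 30/30 has a chance below 0.1%. For ≥30% with SD 1.5, it is Φ(1.9/√2.34) = 89%, so 0.893³⁰ = 3%. For ≥30% with SD 1.0, it is still Φ(1.9/√1.09) = 96.6%, so 0.966³⁰ = 35%.

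**The case against.** A reader might infer that at the trial's own planned response most ≥50% analyses would fail and a large effect would nearly always be missed. The documents do not support that. One route to it assumes a reduction proportional to a baseline of 5.0±1.0, which gives 82% separated and power of 14.5% (Wald) against 93.5% (Firth). But a slope of 3.4/5.0 = 0.68 with residual SD 0.3 makes the acupuncture change SD √(0.68² + 0.3²) = 0.74, more than twice the planned 0.3. Another route needs every patient to start at almost exactly 5.0. That figure is a background average for TMD patients, not a planning value.

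Nor do separation and a large missed effect sit together on ≥30% at mean 5.0. Separation is near certain there, but the true difference is a few points and no method would detect it reliably.

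It is also fair that Wald inference is inferred: neither document states the interval type, and the imputation text concerns weekly pain. A profile-likelihood interval would have a finite lower limit, and the likelihood-ratio test keeps 74-99% power for ≥50% at mean 5.0 with SD 0 to 1.5. Arm percentages are reported too, so 30/30 would be visible. These are secondary outcomes, and the primary analysis is untouched.

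These points limit the size of the problem but do not remove it. A profile interval is not specified, and with 30/30 it would still leave an infinite estimate and upper limit.

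**Conclusion.** The point holds in a conditional form. If the planned changes are right, the ≥30% odds ratio and its CI will almost certainly not be reportable; this holds across assumed baseline means of 5 to 7. For ≥50%, separation ranges from rare to likely, depending on the mean, spread and correlation of baseline pain, none of which the documents give. At 5.0±1.0 a Wald interval would cost about 19 points of power (67% versus 86%) with independent change, or about 51 points (37% versus 88%) at correlation 0.4. From a mean of 5.5 with SD 1.0 and independent change there is little loss. Everything rests on the pilot SDs: the ≥50% problem largely goes at change SDs of about 1.0, and the ≥30% problem at about 1.5. A method that stays finite should be named before unblinding.

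**What to change.** In SAP 8.3.2 and 8.4.3 and protocol 12.6.3, replace the ordinary logistic model with Firth penalised logistic regression, same covariates, with a profile penalised-likelihood 95% CI. Also report the covariate-standardised difference in responder proportions with a 95% CI, using a score-type interval if both arms are at 100%. With imputed data, pool the risk difference or the finite Firth estimates; nothing more elaborate is needed.

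This costs a few sentences of SAP text and a common software option, with no new data or patients. The downside is slight shrinkage of the odds ratio towards 1. Where separation is absent, power is essentially the same (20.2% Firth versus 20.8% Wald for ≥50% at change SD 1.5), and in simulated trials with no effect Firth rejected in 1% to 5%.
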